#### Sample size calculation

To date, there are no published studies on the effect of baclofen on relapse in GHB dependent patients. Therefore, we used the results of previous studies on the effect of baclofen in alcohol dependent patients and our previous work on GHB dependence, in order to estimate the required sample size. Two RCTs showed that baclofen was superior to placebo in increasing abstinence rates in alcohol dependent patients: 70% (14 out of 20) versus 21% (4 out of 19) within a period of 30 days [29] and 71% (30 out of 42 p) versus 29% (14 out of 42) within a period of 12 weeks [30]. These results indicate a potential increase in abstinence of 42–49% with baclofen treatment for alcohol dependence. Results of the previous national GHB project stated that 36% of the patients succeeded to avoid relapse in GHB within a period of 3 months after detoxification without any medical interventions [20]. Therefore, we will consider a percentage of importance difference in baclofen effect in the GHB dependent participants of 34% between the Baclofen + TAU group and the TAU only or the matched control group with an expected abstinence rate with baclofen of 70% as in the alcohol studies and of 36% without baclofen.

We used the following formula comparing two proportions to calculate the sample size, n = [(Zα/2 + Zβ)^2^ × {(p1 (1-p1) + (p2 (1-p2))}] / (p1 - p2)^2^, n = [(1.96+ 0.84)^2^ × {(0.7 (1–0.7) + (0.36 (1–0.36))}] / (0.34)^2^, according to [name] sample size calculator, Exeter Initiative for Statistics. The calculation estimates that the minimal total samples size of 30 patients per group would be sufficient to detect a clinical difference of 34% in two-tailed z-test of proportions (α = 0.05, β=0.80). In the alcohol studies and our previous work with GHB inpatients an attrition rate of 13–15% was reported. We anticipate a slightly higher drop-out rate of 25%, due to the outpatient component of the baclofen treatment. Therefore we will include 40 participants in the baclofen treatment group.

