#### Treatment as usual (TAU)

Patients included in the current study will undergo the usual treatment provided by their addiction treatment center (TAU). These can vary from short individual behavioral treatment intervention, inpatient treatment, Community reinforcement therapy, or extensive multidimensional therapy (like MDFT) with attention to psychological, social, relation, financial, and medical problems. During the study the psychological interventions applied will be monitored. For the historical control group, reports on the adjunct psychological treatment interventions applied are unavailable.

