### Statistical analyses

Descriptive analysis will be executed for all measurements and will include the mean, SD and frequencies of events with confidence intervals. Descriptive statistics will be used to compare the basic characteristics of the participants in the experimental group and the control groups. To assess any difference in relapse rates between the experimental group and the control groups (TAU group and matched historical group) at 3 month after detoxification Pearson Chi-squared test will be used for the dichotomous abstinence rates. ANOVA will be carried out on continuous variables, such as the total number of abstinent days, the maximum duration of continued abstinence, time before relapse (relapse defined as ≥ 3 times GHB use per day, for 2 subsequent days), and level of substance use over a period of 3 months. At 6 months period participants who continued baclofen will be compared to those who have stopped with baclofen (after 3 month) on relapse into GHB abuse or abstinence corrected for craving. The numbers of patients maintaining abstinence will be analysed with the intention-to-treat principles. The difference in craving will be analysed by MANCOVA at 3 months between groups (abstinent experimental versus abstinent TAU or relapsed TAU) with DDQ and VAS craving as dependent variables and corrected for craving levels immediately after detoxification. The change in craving in time during the baclofen treatment will be analysed via repeated measures MANOVA. By means of MANCOVA at 6 months after detoxification the difference in craving among participants who are still using baclofen and those who have discontinued baclofen will be analysed corrected for craving after 3 months. The effect of baclofen on the psychiatric symptoms levels (DASS, MINI) and also quality of life (EQ–5D) will be analyzed similarly as for craving at 3 and 6 months. The effects of the different TAU approaches as potential confounders will be tested in a sensitivity analyses (changing one-factor-at-a-time) in an linear regression including TAU per center as covariates.

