The current study does have several limitations. First, the study is not randomized, nor placebo controlled. However, we will compare patients receiving baclofen with a control group matched for gender, age and the pattern of GHB use, in order to control for potential confounding factors. Second, the accompanying treatment as usual (TAU) is not identical in all participating addiction care facilities. This may confound our results. The impact of TAU will be checked with a sensitivity analysis compare patients’ results from the different centers conforming the add-on baclofen effect.

Given these methodological limitations the current study should be considered explorative in nature. Given the currently rather limited information from both preclinical and clinical studies of GHB such an explorative approach seems justified. We would also like to test the GHB substitution effect of baclofen (as a GABA-B agonist) hypothesis. It is important to evaluate of this effect is clinically recognized and obvious for the participants, and may define placebo use as non-beneficial. We need to be able to determine the margins of the required treatment dose. All forgoing justify this setup of an open label trail before a large placebo controlled randomized trial.

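### The check for confounding by treatment as usual is worded as one factor at a time; if followed, it can leave substantial confounding that joint entry would remove

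*Protocol article*

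**What the plan says.** All places are in the protocol article.

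- **Statistical analyses** treats the different TAU approaches as potential confounders and plans to test them in "sensitivity analyses (changing one-factor-at-a-time) in an linear regression including TAU per center as covariates".
- **Discussion** (limitations) concedes that TAU is not identical across facilities and may confound the results. It answers: "The impact of TAU will be checked with a sensitivity analysis", comparing results between centres in support of the add-on effect of baclofen.
- **Treatment as usual (TAU)** describes the content: "These can vary from short individual behavioral treatment intervention, inpatient treatment, Community reinforcement therapy, or extensive multidimensional therapy (like MDFT"). The interventions will be monitored during the study. For the historical controls no such reports exist.
- **Study design** has six facilities and assigns patients by eligibility and their own preference.

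Nothing else described deals with TAU. The 3-month abstinence comparison is a Pearson chi-squared test, the covariates named for all analyses are socio-demographic, and the historical controls are matched on age, gender, GHB use and detoxification attempts.

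**The concern.** Four forms of TAU are named. A model that contains treatment group and an indicator for one form compares that form with all the others pooled. If the two groups differ in their mix of the pooled forms, and those forms differ in abstinence, the baclofen coefficient carries that difference. Running the model again with another single indicator moves the problem to a different set of pooled forms. No model in the series removes the whole of the TAU confounding, although the monitored data would allow it.

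This matters because allocation is by preference and the Discussion cites this analysis when it addresses TAU. A baclofen estimate that survives such a check could be partly or wholly a TAU difference. The problem does not depend on whether TAU is recorded per centre or per patient.

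**Working it through.** **Inputs from the article.** Group size: (1.96 + 0.84)² × (0.70 × 0.30 + 0.36 × 0.64) / 0.34² = 7.84 × 0.4404 / 0.1156 = 29.87, so 30 per group. With 25% drop-out, 30 / 0.75 = 40, which agrees with "we will include 40 participants in the baclofen treatment group" and with the total of 80 in the Abstract. These figures reproduce and this point does not affect them. The article gives no figure for TAU confounding.

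**Assumed inputs.** No true baclofen effect. Four exclusive TAU forms A to D with 3-month abstinence of 20%, 35%, 45% and 60%. Mix of forms 10/20/30/40% in the baclofen group and 40/30/20/10% in the TAU-only group.

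**Crude difference.**
- Baclofen: 2.0 + 7.0 + 13.5 + 24.0 = 46.5%.
- TAU-only: 8.0 + 10.5 + 9.0 + 6.0 = 33.5%.
- Difference: 13.0 points, all of it due to TAU.

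**One form at a time.** With equal groups, the coefficient for treatment group in a linear model with one indicator is Σ w·d / Σ w over the two strata (that form; all others). Here d is the within-stratum difference in abstinence and w = m₁m₀ / (m₁ + m₀), where m₁ and m₀ are the shares of each group in the stratum. Within a single form d = 0.

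| Form entered | Others pooled: baclofen vs TAU-only | d | w (others) | w (form) | Points left | Share of 13.0 |
|---|---|---|---|---|---|---|
| A | 49.44% vs 42.50% | 6.94 | 0.360 | 0.080 | 5.7 | 44% |
| B | 49.38% vs 32.86% | 16.52 | 0.373 | 0.120 | 12.5 | 96% |
| C | 47.14% vs 30.63% | 16.52 | 0.373 | 0.120 | 12.5 | 96% |
| D | 37.50% vs 30.56% | 6.94 | 0.360 | 0.080 | 5.7 | 44% |

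For A: 0.360 × 6.94 / (0.360 + 0.080) = 5.7.

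**All forms together.** Every within-form difference is 0, so 0 points are left.

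**Half the imbalance** (17.5/22.5/27.5/32.5% against the reverse). The crude difference is 6.5 points. Single entry leaves 2.6 (A or D) or 6.2 (B or C), that is 40% or 95%. Joint entry leaves 0.

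**Other structures** (large-sample regressions, no true effect, assumed associations), share of the crude difference left by single entry:
- Equal independent binary factors: 0% with one factor, 63% with two, 73% with three, 79% with four, 83% with five.
- Four factors with latent correlation 0.3, 0.6 and 0.9: 67%, 55% and 35%.
- One dominant factor among four (weight 0.5, 0.7, 0.9): 31%, 10% and 1% in the model that contains it, 94% to 100% in the others.
- One six-level categorical TAU variable: 65% to 99% one indicator at a time, about 0% entered whole.

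**False positives.**

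| Simulated setting, no true effect | Crude | Single models | All four single models significant | Joint |
|---|---|---|---|---|
| Four forms as tabulated, 40 per group, false benefit (nominal 2.5%) | 23% | 8% to 21% each | about 5% | about 3% |
| Four strong independent factors, n = 80, two-sided 5% | 45% | – | 19% | 6% |
| Four weak independent factors, n = 80, two-sided 5% | 7% | – | 4% | 5% |

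**Cost in precision** (tabulated case, 40 per group). Unadjusted standard error: √[(0.465 × 0.535 + 0.335 × 0.665) / 40] = 0.109. Simulated standard error with TAU forms entered jointly: about 0.120. With centre added: about 0.124.

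**The case against.** The strongest reply is that the sentence does not clearly prescribe single entry. It speaks of one regression with covariates in the plural, and the bracketed words can mean varying one element of a joint model at a time. If TAU per centre enters whole, about none of the TAU confounding remains. This stands: single entry is one reading. It does not clear the text, because on the joint reading the bracketed rule says something else and a reader cannot tell which applies. Nor is this only detail that an article leaves to a fuller document, since the article states the method.

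A reader might infer more than the document supports:

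- **That single entry leaves most of the confounding.** This is not general. The best single models in the illustration leave 40% to 44%, and across structures the share runs from 0% to 100%.
- **That the plan takes small shifts as proof of robustness.** No decision rule is stated, and a fall from 13.0 to 5.7 points would be noticed.
- **That the chance of false confirmation is 8% to 21%.** Those are rates for each model alone. If the effect must survive all four, the rate is about 5% against 3%, and with weak associations there is no excess.

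It is also fair that this is a sensitivity analysis in a study that calls itself explorative and looks ahead to randomised trials. Joint entry has limits too: four forms and six centres take 3 + 5 = 8 indicators among 80 patients, or 60 after 25% drop-out, and TAU may be largely fixed by centre.

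**Conclusion.** The point holds as a defect in a stated method. Followed as worded, the only TAU check can leave substantial confounding that joint entry would remove: 40% to 96% of the crude difference in the illustration, against 0%. If joint entry was meant, the sentence contradicts itself. Either way it needs correcting.

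The size rests on assumed abstinence rates and mixes of TAU. The actual share depends on the number, coding and correlation of the TAU factors, and the inflation of false positives is small when associations are weak. The zero under joint entry assumes that TAU is the only confounder and is recorded well. The document does not support saying that the check will fail or that a baclofen effect will be falsely confirmed. The correction is worth making and does not touch the sample size.

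**What to change.** In Statistical analyses, delete the bracketed one-factor-at-a-time rule and specify the following for the comparison with concurrent TAU-only patients:

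- One pre-specified model with treatment group and TAU approach entered together, TAU as one categorical factor, or as joint indicators if a patient can receive more than one form.
- Centre added where it is not collinear with TAU, with sparse categories collapsed by a rule set in advance.
- Logistic regression for abstinence and linear regression for the continuous outcomes. The present sentence names only linear regression.
- The adjusted baclofen estimate with its 95% CI reported beside the unadjusted one, and the Discussion's statement on the add-on effect based on the adjusted estimate.
- A statement that the historical-control comparison cannot be adjusted for TAU, because those data are unavailable.

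The cost is a few sentences, using data already to be monitored. The downside is a somewhat wider confidence interval at about 80 patients. In the tabulated case the standard error rises from 0.109 to about 0.124, a factor of 0.124 / 0.109 = 1.14, of which centre accounts for the step from 0.120 to 0.124. The increase would be larger if centre and TAU overlap strongly, so the model must be kept small.

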Safety of baclofen, as assessed by the number and intensity of reported side effects, will be analyzed in the following categories: acceptable or unacceptable adverse effect, clinically significant deterioration, and relocation. In all analyses socio-demographic characteristics such as age and gender will be considered as co-variates in the analysis. Two-sided p-value of > .05 is considered statistically significant. The statistical software package SPSS will be used for all the computations.

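### The significance rule is printed backwards, power is labelled as β, and 30 evaluable patients per group give about 77% power, not 80%

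*Protocol article*

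**What the plan says.** The only significance criterion in the Statistical analyses section of the protocol article reads: "Two-sided p-value of > .05 is considered statistically significant". The same section plans a Pearson chi-squared test for the dichotomous abstinence rates at three months and adds: "The numbers of patients maintaining abstinence will be analysed with the intention-to-treat principles".

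The Sample size calculation section introduces its formula with "We used the following formula comparing two proportions to calculate the sample size". The formula uses the unpooled variance, with 1.96 for Zα/2 and 0.84 for Zβ. The planning rates are an "expected abstinence rate with baclofen of 70% as in the alcohol studies and of 36% without baclofen". The section concludes that a "minimal total samples size of 30 patients per group" is "sufficient to detect a clinical difference of 34% in two-tailed z-test of proportions", with error rates given as "α = 0.05, β=0.80". Allowing for 25% drop-out, it sets the baclofen group at 40. The Abstract gives a total of 80.

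**The concern.** Two statements about error rates are wrong as printed. A rule that calls p-values above 0.05 significant is the reverse of a test at α = 0.05. A β of 0.80 means 20% power, which is not what the formula beside it uses.

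A smaller third matter is that the 80% power is a normal-approximation figure for a small trial, and exact calculation gives somewhat less.

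The threshold applies to every test in the study, and the power statement is the only justification given for its size. Both should therefore be correct in print, even though the Discussion section calls the study exploratory.

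**Working it through.** **Inputs** (protocol article, Sample size calculation): p1 = 0.70, p2 = 0.36, difference 0.34, Zα/2 = 1.96, Zβ = 0.84, 30 per group, 25% drop-out, 40 in the baclofen group. From Statistical analyses: Pearson chi-squared test. From the Abstract: total n = 80.

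**1. The plan's own sample size.**
- Variance term: 0.70 × 0.30 + 0.36 × 0.64 = 0.2100 + 0.2304 = 0.4404.
- n = (1.96 + 0.84)² × 0.4404 / 0.34² = 7.84 × 0.4404 / 0.1156 = 29.87, rounded up to 30. This reproduces.
- Drop-out: 30 / (1 − 0.25) = 40. This also reproduces.

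**2. The β label.** A Zβ of +0.84 corresponds to power 0.80, so β = 0.20. If β really were 0.80, Zβ would be −0.84 and n = (1.96 − 0.84)² × 0.4404 / 0.1156 = 1.2544 × 0.4404 / 0.1156 = 4.78, or 5 per group. The stated 30 follows only from 80% power, so the label is wrong and the calculation is not.

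**3. The significance rule.** The sample size section uses two-tailed α = 0.05 (Zα/2 = 1.96), which means rejecting when p is below 0.05. The printed rule points the other way. To show what the words mean if taken literally, with 30 per group and the Pearson test by exact enumeration:
- No effect (36% v 36%): p < 0.05 has probability 0.048, so the printed rule would declare significance in about 95% of trials.
- Planned effect (70% v 36%): p < 0.05 has probability 0.773, so the printed rule would declare significance in about 23%.

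**4. Power at 30 evaluable per group, 70% v 36%.**
- Unpooled normal approximation (the plan's formula): Φ(0.34 × √30 / √0.4404 − 1.96) = Φ(0.846) = 80.1%.
- Pooled normal approximation: the mean rate is 0.53 and 2 × 0.53 × 0.47 = 0.4982, so Φ[(0.34 × √30 − 1.96 × √0.4982) / √0.4404] = Φ(0.722) = 76.5%.
- Exact power (binomial probabilities summed over all tables with p < 0.05): Pearson 77.3%, unpooled z-test 77.4%.

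**5. Size needed for 80%.**
- Pooled formula: (1.96 × √0.4982 + 0.84 × √0.4404)² / 0.1156 = 32.6, or 33 per group.
- Exact Pearson power:

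| Per group | Exact power |
|---|---|
| 30 | 77.3% |
| 31 | 79.6% |
| 32 | 81.7% |
| 33 | 83.6% |
| 34 | 80.5% |
| 40 | 88.7% |

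Exact power is not strictly increasing because the data are discrete, but it stays above 80% at every size from 32 to 40.

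**The case against.** The strongest reply is that the two misprints resolve themselves. Two-tailed testing, α = 0.05, 1.96 and 0.84 all stand in the sample size section, the 30 per group reproduces, and no analyst is likely to call p > 0.05 significant. This largely stands. They are almost certainly slips and change neither the design nor the sample size, and the 95% and 23% above describe the printed words, not what the trial would do. It does not remove the need to correct a printed decision rule that says the opposite of what is meant.

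A second reply is that a standard published formula is a legitimate choice, especially in an exploratory study. That also stands: 30 is not an arithmetic error. The remaining point is only that the approximation overstates power by about 3 percentage points.

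Two stronger readings are tempting, and the documents do not support them.

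- A reader might infer that power is lost because the trial was sized with an unpooled variance and will be tested with Pearson's pooled one. Exact enumeration gives 77.3% and 77.4% for the two tests, so the choice of test costs practically nothing. The gap comes from the normal approximation and the discreteness of the data.
- A reader might infer that intention-to-treat analysis undermines the power, because the inflation to 40 treats drop-outs as lost while the analysis keeps them in. If 25% in both groups dropped out and counted as relapsed, the rates would be 0.75 × 70% = 52.5% and 0.75 × 36% = 27%, and exact power at 40 per group would be 66%. With 15% in both groups (59.5% v 30.6%) it would be 76.5%. With the 70% and 36% unchanged it is 88.7%. These are illustrations only. The protocol article links the 25% to the outpatient part of baclofen treatment and does not assign it to controls. It fixes 40 only for the baclofen group. How drop-outs are counted is commonly left to the full protocol or the analysis plan.

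**Conclusion.** The point holds in three parts of unequal weight. The significance rule is inverted and contradicts the α stated elsewhere in the same article; this is a plain error in the criterion for every test and must be corrected. The β of 0.80 is a mislabelled power of 0.80. The power at 30 evaluable patients per group is about 77%, against the stated 80%, a shortfall equivalent to two patients per group by exact enumeration or three by the pooled formula.

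The power figures assume equal groups, true abstinence of 70% and 36%, and a two-sided 5% Pearson test without continuity correction. The article does not support saying that the sample size was miscalculated, that the planned test is weaker than the one used for sizing, or that the trial is underpowered under intention to treat. If 40 per group are analysed and the planning rates hold, power is about 89%; the control figure is inferred from 80 − 40 = 40.

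**What to change.** - In Statistical analyses, state that a two-sided p < 0.05 is considered statistically significant.
- In Sample size calculation, replace the β of 0.80 with power = 0.80 (β = 0.20) as the target used in the formula.
- In the same section, add that the exact power of the planned Pearson test at 70% v 36% is about 77% with 30 evaluable per group. If it helps the reader, add that it is about 89% if 40 per group are analysed at the same rates.

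This is a change of text only. It needs no more patients and no change to the design or the planned test. The only downside is a slightly less favourable stated power.

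### The significance rule in the protocol article has its inequality reversed: almost certainly a typographical error, minor, but it should be corrected

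*Protocol article*

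**What the plan says.** The protocol article's Statistical analyses section first lists the tests: a Pearson chi-squared test for abstinence at three months, ANOVA for the continuous measures of GHB use, MANCOVA and repeated measures MANOVA for craving (with similar analyses for psychiatric symptoms and quality of life), and a regression as sensitivity analysis. It then closes with one general rule: "Two-sided p-value of > .05 is considered statistically significant".

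The Sample size calculation section works at the conventional level. It describes a "two-tailed z-test of proportions (α = 0.05, β=0.80" and enters the standard normal values as "n = [(1.96+ 0.84)^2^ × {(0.7 (1–0.7) + (0.36 (1–0.36))}] / (0.34)^2". The rates behind it are an "expected abstinence rate with baclofen of 70% as in the alcohol studies and of 36% without baclofen". The stated result is that a "minimal total samples size of 30 patients per group would be sufficient to detect a clinical difference of 34" percentage points. No other section gives a decision rule or corrects the one in the Statistical analyses section.

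**The concern.** A two-sided test at α = 0.05 declares significance when p falls below .05. The printed sentence declares it when p lies above .05. The planning section and the analysis section therefore cannot both stand as written.

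The sentence is attached to no single endpoint. It follows the full list of tests, and no other threshold is given for any of them, so it covers the primary abstinence comparison and the secondary outcomes alike. A prespecified threshold is also what a later reader uses to check reported conclusions against the plan. As printed, a result reported as significant at p < .05 would formally depart from the published rule.

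**Working it through.** **Inputs, all from the protocol article**
- Rule as printed: significant if two-sided p > .05 (Statistical analyses).
- Planning level: two-tailed, α = 0.05, critical value 1.96 (Sample size calculation).
- Power: the article writes β = 0.80, but its formula uses 0.84, the normal value for 80% power. I read it as 80% power.
- Abstinence: 70% with baclofen, 36% without.
- Size: 30 per group, and 40 in the baclofen group after allowing for 25% drop-out. The abstract gives 80 patients in total.

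**Step 1. Reproduce the stated sample size**

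n = (1.96 + 0.84)² × [0.70 × 0.30 + 0.36 × 0.64] / 0.34²

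= 7.84 × (0.2100 + 0.2304) / 0.1156

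= 3.4527 / 0.1156 = 29.87, rounded up to 30.

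The drop-out allowance gives 30 / (1 − 0.25) = 40. Both figures reproduce. The value 1.96 is the boundary of the region |z| > 1.96, which is the same as two-sided p < .05. The sample size was thus built on the usual rule.

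**Step 2. What the printed rule implies if taken literally**

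Nominal values:
- No true effect: P(p > .05) = 1 − 0.05 = 0.95.
- True effect at the planned power: P(p > .05) = 1 − 0.80 = 0.20.

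Exact values come from enumerating all binomial outcomes for the uncorrected Pearson chi-squared test, with both rates at 36% for the null and 70% against 36% for the planned effect. Each literal-rule figure is one minus the usual-rule figure.

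| Per group | Rule | Called significant, no effect | Called significant, 70% v 36% |
|---|---|---|---|
| 30 | p < .05 (intended) | 4.8% | 77.3% |
| 30 | p > .05 (as printed) | 95.2% | 22.7% |
| 40 | p < .05 (intended) | 4.9% | 88.7% |
| 40 | p > .05 (as printed) | 95.1% | 11.3% |

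The rows for 40 per group assume that the 80 patients split evenly and that all of them contribute to the comparison.

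**Step 3. Could it be a fault in the text rather than in the plan?**

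Other inequality signs in the article come through sensibly: the liver enzyme and bilirubin limits in the exclusion criteria, the relapse definition in the Statistical analyses section, and the per-administration dose bound in the Discussion. A fault in reading the PDF cannot be excluded entirely, but nothing points to one.

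**The case against.** The strongest reply is that nobody will apply this sentence. The sample size section shows what was intended, only one reading agrees with it, and SPSS p-values would be read in the usual way. The article also calls the study explorative and places it before a larger randomised placebo-controlled trial. On this view the authors mistyped a sign and did not choose a bad analysis. That stands, and it is why the point is minor.

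A reader might go further than the article allows in three ways.

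- **That the trial will report chance findings as positive and miss real ones.** The article does not support this. The 95% and 20 to 23% figures are complements of the ordinary error rates and would arise only if every p-value were deliberately read backwards.
- **That the 20% figure applies to all tests.** It belongs only to the one comparison that was sized, and it moves with the numbers analysed (22.7% at 30 per group, 11.3% at 40). The article states no power for the other outcomes.
- **That a statistical analysis plan carries the same error.** No such plan is shown, so nothing can be said about it.

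What the reply does not remove is the error itself. The sentence stands in the operative analysis section, it is wrong as written, and nothing else in the article corrects it.

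**Conclusion.** The inequality in the significance rule is reversed and contradicts the α and critical value used to size the trial. It is almost certainly typographical, since the stated 30 per group follows (29.87) from a critical value that means rejection at p < .05. The expected effect on results is small, on the assumption that the analysts follow the planning section and ordinary practice. The literal text implies about 95% of null results called significant, and about 20 to 23% for 70% against 36% at 30 per group. Severity: minor, but it should be corrected.

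**What to change.** By erratum to the protocol article, change the greater-than sign to a less-than sign in the final paragraph of the Statistical analyses section, so that a two-sided p-value below .05 counts as statistically significant. This brings the rule into line with the Sample size calculation section.

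The cost is one character. The 30 per group, the enrolment of 40 in the baclofen group, the choice of tests and the conduct of the study all stay as they are.
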